Although condition-specific risk prediction tools have been successfully developed and applied to conditions such as diabetes and coronary heart disease [17,18], there is less evidence regarding generic population-based tools. Predictive models, such as Patients at Risk of Readmission (PARR) and Scottish Patients At Risk of Readmission and Admission (SPARRA), have been used successfully in the UK National Health Service (NHS) to stratify patients into risk levels [19,20]. The models used in England and Scotland focussed only on those at most risk – on patients over 65 years in Scotland and on the sickest 1% or 2% in England. Steps to include the whole population were later included in the English Combined Predictive Model and are now being taken in Wales through the development of a predictive risk stratification model (Prism) [21]. Prism calculates a risk score of between 0 (no risk) and 100 (very high risk), based on patient demographics and data from primary and secondary care record systems. Patients are stratified into four levels based on their individual risk of having an emergency admission to hospital during the following year. This reflects the Welsh Chronic Conditions Management policy focus to prevent disease onset and deterioration across the population [6]. The performance of Prism appears comparable to or better than the English model [21] and an independent pilot evaluation [22] has indicated potential for impact. However, many practical questions remain about how it will be adopted and used by service providers for each risk stratum [23].

Although stratification will not in itself lead to improvements in service delivery, it aims to stimulate the planning and targeting of care. Thus it is intended to influence health care delivery and ultimately patient outcomes. Recent policy documents in the UK and internationally have generated expectations that, in future, health communities will routinely stratify their populations according to risk of hospital admission [1,2,6,24,25]. To inform future policy and practice we designed a prospective evaluation of the implementation of Prism and present the study protocol in this article.

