### Prism

Prism is a web-based predictive risk tool commissioned by the Welsh Government that stratifies a General Practice population into four levels based on the individual risk of an emergency admission to hospital in the following 12 months. Prism was developed and checked using 300,000 (10% of the Welsh population) anonymised GP and hospital records from which 37 variables with the highest predictive power were selected. The variables used to develop Prism were drawn from routinely available data on inpatient, outpatient and primary care episodes and from the Welsh Index of Multiple Deprivation (http://wales.gov.uk/topics/statistics/theme/wimd/wimdstatement/;jsessionid=36B68DFE653760993E3E03966D7760B8?lang=en), which includes data on employment, income, housing, environment, education and health. To enable GP practices, individually or collectively, to plan workforce and resource allocation, each stratum represents a variable percentage of the practice population (which can be changed at the practice level depending on how they want to look at their own population data) with the top stratum (level 4) of patients being at highest risk of an emergency admission in the following year. The theoretical basis of the model is that patients in each of the four strata need very different targeted resources: level 4 requires individual case management, level 3 requires disease management on a population basis, level 2 requires supported self-care and level 1 needs prevention of illness and promotion of health and wellbeing.

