#### Secondary outcomes

Primary care service use—GP practice events/event days.

Accident and emergency attendances.

Community care service use.

Secondary care inpatient and outpatient episodes (including length of stays).

NHS implementation costs.

Number of Prism users.

Pattern (including frequency) of Prism use.

Patient satisfaction.

Predicted emergency admissions.

Health-related quality of life (SF-12).

We will also explore in detail within the intervention group and at other sites:

• Technical performance of the Prism tool—predicted compared to actual emergency admissions to hospital.

• Practitioner, commissioner and policy maker views about Prism implementation, adoption and effects.

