	Focus group	Local health services managers and community staff managers (*n* = 1)	18 months
	Interviews	Health service managers from ABMU (*n* = 3)	18 months
	Structured telephone interviews	Prism users from all participating practices (*n* = up to 40)	18 months
5. Assess the effect of Prism on patient satisfaction	Questionnaire data: Quality of Care Monitor	Random sample of patients from participating practices (*n* = 800 at each time point)	Baseline
			6 months
			18 months
6. Assess the technical performance of Prism	Prism data	Prism risk data for patients at participating practices	Baseline
			6 months
			18 months
	Anonymised routine linked data	Routine health data	Baseline
			6 months
			18 months
	Structured telephone interviews	Prism users from all participating practices (up to 40)	18 months

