#### Anonymised linked data

We will use routine data from the Secure Anonymised Information Linkage (SAIL) databank [30] to compare services delivered to patients (emergency, acute, primary, community and social care) across the spectrum of risk between intervention and control practices. SAIL includes routine Welsh hospital data such as emergency admissions (Emergency Department Data Set; EDDS), secondary care (Patient Episode Database for Wales, PEDW) and GP practice data. We will run the Prism algorithm within the SAIL databank to generate risk scores linked to health service usage data for all study patients who do not dissent.

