The perspective of NHS Wales and personal social services will be adopted for the health economic analysis. The costs of implementing Prism in intervention and control sites will be derived from interviews with GP practice staff and with members of the main trial team (e.g. training resources). The costs associated with resulting changes in care processes will be derived from routine data collected by the Prism system from SAIL and by patient-reported information collected by the CSRI questionnaire. Costs will be presented in a tabular format reporting the estimated resource quantities and unit costs attached. The estimation of the size of the differences (means and standard deviations) in resource use between intervention and control sites within each of the four risk strata and overall will be calculated and valued in monetary terms using published unit costs (with year of reported cost reported) [36]. The primary health economic analysis will be the calculation of the incremental cost per emergency admission avoided in a cost-effectiveness analysis and will produce a tabular representation of costs versus changes in primary and secondary outcomes in a cost-consequences analysis. The incremental cost per quality-adjusted life year (cost/QALY) will be calculated in a cost-utility analysis using SF-6D utility scores derived from SF-12 patient questionnaire data. A series of univariate sensitivity analyses will be carried out to determine the extent to which changes in the basic assumptions of the economic analysis affect the incremental cost-effectiveness ratio.

We will record and transcribe focus groups and interviews and analyse them thematically. This is a systematic and transparent method of analysis that generates themes from the explicit and implicit ideas contained in the original accounts of participants. One researcher will lead the analysis with two others independently supporting key stages of coding, generating themes and interpretation and encouraging a critical stance to test and confirm findings [35,37,38].

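### By-risk comparisons leave the date of Prism level open and state no time adjustment within level, so either dating choice can bias the by-level results

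*Protocol article*

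**What the plan says.** **The comparison.** The Analysis section values differences in resource use, as means and standard deviations, "between intervention and control sites within each of the four risk strata and overall". It states no date for stratum membership and no time term for this comparison. Objective 1 also concerns services across the range of risk, with emergency admissions as its focus.

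**The score.** The Prism section says of the model's inputs: "The variables used to develop Prism were drawn from routinely available data on inpatient, outpatient and primary care episodes". The Background says of stratification that "it aims to stimulate the planning and targeting of care". The Anonymised linked data section adds: "We will run the Prism algorithm within the SAIL databank to generate risk scores linked to health service usage data for all study patients" (those who do not dissent). It gives no index date for that run.

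**Repeat measurement.** In Table 1, the objective 1 row lists linked routine data, expressly including Prism data, at baseline, 6 and 18 months. The objective 6 row lists "Prism risk data for patients at participating practices" at the same times.

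**Cut-offs.** Table 2 gives default score ranges for the four levels. The Prism section says the share of patients in each stratum is something "which can be changed at the practice level depending on how they want to look at their own population data".

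**Predicted admissions.** The Outcomes section introduces its list as comparisons between intervention and control groups after activation. The secondary list includes "Predicted emergency admissions".

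**A safeguard elsewhere.** For technical performance, Analysis uses baseline and control-phase data and fits an indicator for adoption. Nothing comparable is written for the by-level comparisons.

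**The concern.** A subgroup variable in a randomised comparison should be fixed before the intervention can act on it. The Prism score draws on the same kinds of service record that Prism is meant to alter. After go-live, extra case-finding and visits can move a patient up a level, and avoided admissions can move one down. Patients in a given level under Prism are then not the same kind of patients as those in that level under control.

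Fixing level at baseline removes that problem but exposes another. Patients selected for a high score tend to have lower use later. In a stepped wedge every practice contributes control time first and Prism time second, so that natural fall lands mostly on the Prism side. A difference in means within level, with no time term, would credit it to Prism.

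At stake are the stratum-specific resource and cost differences, which would tell services where on the risk spectrum Prism pays. Predicted admissions compared between groups after activation share the first problem: fuller recording can raise them while true risk is unchanged or falling.

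**Working it through.** **1. Plan's own figure.** The plan gives no figure for this bias. Its only number for patients at a defined risk is 80% power for a 15% change. Taking 15% as percentage points, 1:1 allocation and no clustering, the smallest stratum has 0.15 × 2,400 = 360 respondents, 180 per condition. Power for 0.425 against 0.575 is then 0.815, so the figure reproduces. It concerns precision and is not affected by this point.

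**2. How far apart control and Prism time lie.** Inputs from the article: 11 practice clusters, and a last data point 18 months after the first practice goes live. Assumed: equal clusters, with go-live evenly spaced at g = R·k/10 (k = 0 to 10) over R = 6 or 12 months. The text gives no roll-out length.

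- Mean control month = Σg² / (2Σg) = (R/10) × 385 / (2 × 55) = 0.35R, which is 2.1 or 4.2.
- Mean Prism month = Σ(18² − g²) / (2Σ(18 − g)).
  - R = 6: (3,564 − 138.6) / (2 × 165) = 10.38.
  - R = 12: (3,564 − 554.4) / (2 × 132) = 11.40.
- Gap = 8.28 or 7.20 months.

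If the admission rate in baseline level 4 falls naturally by a fraction d per year, the spurious reduction without time adjustment is 1 − (1 − d)^(gap/12).

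| Assumed d | R = 12 | R = 6 |
|---|---|---|
| 10% | 6.1% | 7.0% |
| 20% | 12.5% | 14.3% |
| 30% | 19.3% | 21.8% |

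No value of d can be taken from the article.

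**3. Illustrative simulation, true rate ratio 1.00.** It used 400,000 patients, six periods and five crossover steps. The score combined stable risk with recent use, plus an optional recording uplift on the log score after Prism. Level cuts were set at the 80th, 94.5th and 99.5th percentiles of the baseline score. All these settings are assumptions. Adjusted ratios are Mantel-Haenszel by period within level.

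| Level dating | Time handling | L1 | L2 | L3 | L4 |
|---|---|---|---|---|---|
| Updated, no uplift | crude | 0.995 | 0.998 | 1.009 | 0.994 |
| Updated, no uplift | adjusted | 0.998 | 0.995 | 1.000 | 1.044 |
| Updated, uplift 0.25 | crude | 0.925 | 0.862 | 0.879 | 0.903 |
| Updated, uplift 0.25 | adjusted | 0.944 | 0.895 | 0.908 | 0.934 |
| Baseline | crude | 1.023 | 1.022 | 0.933 | 0.806 |
| Baseline | adjusted | 1.003 | 1.010 | 0.973 | 0.989 |

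With uplifts of 0.1 to 0.5, the adjusted ratios for updated levels run from 0.976 down to 0.789. The overall ratio was 1.00 throughout.

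**4. Simulation noise.** The top level holds 0.005 × 400,000 = 2,000 patients, so single values wobble. The uplift enters neither the baseline level nor the outcome, so the four no-effect runs replicate the baseline rows. Top-level crude ratios were 0.806, 0.841, 0.824 and 0.836 (mean 3.307/4 = 0.827). Adjusted ratios were 0.989, 1.027, 0.964 and 0.956 (mean 3.936/4 = 0.984).

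**5. Does the remedy recover a real effect?** With a true ratio of 0.85 and uplift 0.25, baseline levels with period adjustment gave 0.852, 0.853, 0.856 and 0.854. Updated levels with period adjustment gave 0.807, 0.772, 0.802 and 0.807. With the same true ratio and no uplift, updated levels gave 0.944 in the top level, that is, attenuation. The direction of bias under updating therefore depends on which mechanism dominates.

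**6. Why the time term must be level-specific.** The overall rate in the simulation is flat while the top level falls and the lowest rises slightly. A single calendar term shared by all levels has almost nothing to remove, and the drift within level stays.

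**The case against.** The strongest reply is that this is detail a condensed article leaves to the full protocol or SAP. The covariate list includes baseline observations as well as time-varying terms, and collecting scores at 6 and 18 months does not mean that levels are reassigned with them. The authors plainly know that Prism can confound score-based analyses, since they protect the technical-performance assessment. Much of this stands, and it rules out several stronger readings:

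- **That the plan uses Prism-altered levels.** A reader might infer this from Table 1. The article neither says so nor excludes it.
- **That recording bias and regression to the mean combine.** They belong to different choices. In the simulation, updated levels without uplift gave about 1.00, and regression to the mean appeared only with baseline levels and no time adjustment.
- **That practice-set cut-offs enter the analysis.** The text on changing strata describes how practices view their own data. The trial's scores come from a central SAIL run.
- **That level 1 would look harmed.** The simulated crude ratio there is only 1.02.
- **That the main results are compromised.** The primary outcomes, the overall contrast and the primary economic ratio (cost per avoided admission) are not defined by level.

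The reply does not remove the point. What the article does state is a difference in means within level, in a design where Prism time follows control time. It also names post-go-live Prism data as a source for the effect objective and predicted admissions as a between-group outcome. Both obvious ways of dating level can mislead under that description, and a better method is available at little cost.

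**Conclusion.** The point holds as a worthwhile improvement to the by-level (secondary) analyses. Updating levels after go-live biases them if Prism changes recorded risk. Fixing levels at baseline without time adjustment within level biases level 4 through regression to the mean. Neither the size nor the direction for this trial can be derived from the documents. The top-level ratio of 0.81 to 0.84 under no effect, the range 0.98 to 0.79 under updating, and the 6% to 22% in the arithmetic all rest on assumed drift, roll-out or recording uplift. The firmer result is that baseline-dated levels with period adjustment within level brought the ratios back close to the truth, both with and without a real effect. The comparison of predicted admissions between groups is open to the same recording bias, whatever date is chosen for level.

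**What to change.** - For every by-level effect and cost comparison, assign level once, from the Prism algorithm run in SAIL at a single date before the first go-live, using the default ranges of Table 2 for all practices.
- Adjust for calendar period within level (level × period), so that each level's natural course is estimated from practices not yet live.
- Use predicted emergency admissions for technical performance and as a baseline covariate. If they are still compared between groups, label the comparison descriptive and affected by recording.

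The cost is some analysis wording and a fixed date for an algorithm run already planned. The level 4 estimate becomes less precise. Patients who register after the scoring date need a score at registration or drop out of the by-level analysis; the plan should say which.

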### Project management

The trial has been adopted by WWORTH and we will adhere to all relevant WWORTH standard operating procedures (SOPs) in the conduct, management and monitoring of the study. The strategic management of the trial will be the responsibility of a Research Management Group (RMG) meeting quarterly and comprising the Chief Investigator, all co-applicants, all research staff, two service users and two local participating General Practitioners. Operational management will be the responsibility of the Research Team meeting every month and comprising the researchers, clerical support, the Principal Investigator and one of the co-applicants. [name] will be Research Manager responsible for the operational management of the project from day to day. The PI and Research Manager will ensure adherence to the planned timescale and detailed plans for data management and analysis. A data management task and finish group will oversee all data management and analysis issues. The WWORTH SOP on data management will be used to develop a data management plan, outlining details of data entry, coding, security and storage, including any related processes to promote data quality. An independent Trial Steering Committee (TSC) will provide overall supervision for the study and ensure the rigorous conduct of the trial. It will meet twice a year and be made up of an independent chair with an interest in emergency care, an academic in primary care, a consultant in public health, a statistician and two service users (with no previous involvement in the trial). We will adopt the principles outlined in WWORTH’s SOPs on Quality Assurance and independent trial monitoring will be carried out through WWORTH.

### Including service and research users

In accordance with the WWORTH Standard Operating Procedure for Service User Inclusion [39], we have recruited two service users who will actively participate throughout the study as members of the Research Management Group. They were recruited through SUCCESS (Service Users with Chronic Conditions Encouraging Sensible Solutions), a group of patients and carers involved in research linked to the chronic conditions management policy in Wales (http://www.invo.org.uk/posttypeconference/an-alternative-success-model/) The two service user representatives contribute views from the wider SUCCESS group.

### Ethics and dissemination

The Multi-Centre Research Ethics (MREC) Committee for Wales has given full ethical approval for the study (reference 10/MRE09/25). R&D permissions have been granted across Wales. We have received Information Governance Review Panel (IGRP) permission for use of the SAIL databank. We will seek further approval for any proposed changes to the trial design or conduct with the MREC and relevant R&D committees via amendment reports.

We will comply with the CONSORT guidelines [40]. We will present study results at national and international conferences and publish them in peer-reviewed and clinical journals. We have produced a publication plan and authorship agreement for dissemination of the study findings. Only those individuals who fulfil the authorship criteria will be included as authors on final publications.

## Discussion

There is a lack of evidence regarding how well predictive risk tools work in supporting the management of patients. The proposed study will provide information on costs and effects of Prism; how it is used in practice, barriers and facilitators to its implementation; and its perceived value in supporting the management of patients with and at risk of developing chronic conditions. These findings will have UK and international relevance at a time of heightened focus on chronic conditions management and predictive modelling.

## Trial status (August 2013)

The PRISMATIC trial is currently underway and we have now recruited 32 General Practices across the AMB UHB area to take part. Baseline qualitative data collection (staff focus groups and interviews) were carried out between October 2012 and January 2013. Baseline patient questionnaire distribution began in April 2013.

### Consent

Written informed consent was obtained from the patient for the publication of this report and any accompanying images.

## Abbreviations

ABM UHB: Abertawe bro morgannwg university health board; CSQI: Client service receipt inventory; EDDS: Emergency department data set; IGRP: Information governance review panel; NHS: National health service; NWIS: NHS wales informatics service; PEDW: Patient episode database for wales; QALY: Quality-adjusted life year; QCM: Quality of care monitor; SAIL: Secure anonymised information linkage; SOP: Standard operating procedure; WWORTH: West Wales organisation for rigorous trials in health; WAO: Wales audit office.
